## Introduction

### Background and Rationale

Contraceptive care is an essential health service that allows people to achieve their reproductive goals, including the prevention of undesired pregnancy [1]. Selecting contraception is highly personal and, for many, an overwhelming decision due to the sheer number of potential contraceptive methods [2,3]. There are 18 contraceptive methods (hereafter referred to as “methods”) [4] that include nonprescription methods, prescription methods, contraceptive devices, and permanent contraception (tubal surgeries and vasectomy). Contraceptive methods can be short-acting (taken daily or weekly), long-acting (effective for years), or permanent [4]. Each method has a unique benefit and side effect profile (eg, headache and irregular bleeding) that affects the user’s experience and likelihood of method continuation [4]. Contraceptive decision tools help patients understand the full range of methods and weigh their respective pros and cons in the context of their personal values and preferences [5].

People with acute and chronic health conditions, a growing proportion of contraceptive users, face additional and unique information needs [6]. First, they should understand the impact of a specific method on their health conditions; that is, whether a method improves, worsens, or has no impact on disease state or progression. Second, for those who would continue an unplanned pregnancy to childbirth, they should be informed about potential pregnancy-related risks, or lack thereof, in the context of their health conditions. Third, patients should be aware if their medications interact with hormonal contraception [7] or cause birth defects (eg, phenytoin) [8]. Ideally, health care providers should help process this information so that patients can weigh the pros and cons of different methods and select the best method for themselves.

However, studies have shown that people with health conditions inconsistently receive counseling to make informed contraceptive decisions [9-12]. For example, in outpatient settings, 10%-39% of patients report using combined hormonal contraception (CHC) despite having conditions that may preclude the safe use of CHCs [9,11,12]. Patients who cannot use CHCs should be fully informed about non-CHC methods based on their personal needs and preferences.

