It is also important to bear in mind that most people with health conditions are medically eligible to use most methods [13]; that is, the proven or theoretical benefits of using a specific method generally outweigh any risks in the majority of cases. However, fear of side effects and health concerns are among the most common reasons cited for not using the most preferred method or not using any method among US contraceptive candidates in a nationally representative survey [14]. Contraceptive nonuse, defined as not using any method despite wanting to prevent pregnancy, is associated with the highest risk of unplanned pregnancy [15]. The use of any method reduces the risk of pregnancy by 70%-99.9%, depending on the method type [15]. Patients should receive accurate and balanced information about contraceptive-related health risks, including cases where there is no known risk, to prevent unnecessary avoidance of otherwise safe methods.

In prior randomized controlled trials (RCTs), contraceptive decision tools have been associated with improved patient contraceptive knowledge [16,17], improved quality of contraceptive care experience [16], reduced contraceptive decisional conflict [16], or increased use of prescription contraception [17,18], while others showed no significant differences in outcomes [19-21]. These trials primarily enrolled healthy young adults or adolescents [16,19,20] and did not address clinician knowledge regarding contraceptive use for patients with health conditions.

However, evidence-based clinical guidelines for contraceptive use by people with health conditions do exist. The Centers for Disease Control and Prevention (CDC) United States Medical Eligibility Criteria (US MEC) summarizes evidence-based and expert-informed recommendations for the safe use of contraceptive methods in the context of more than 60 health conditions and characteristics [13]. To distill the 124-page document for clinical use, the US MEC content is available as a free smartphone app and a downloadable color-coded PDF chart summary [22,23]. However, studies show that the US MEC is underused by clinicians, particularly in primary care [24-27] settings. A decision tool that engages both patients and their clinicians is a novel yet unexplored approach to promote informed contraceptive decision-making and use in the context of health conditions.

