### Research Aims and Hypotheses

#### Quantitative Aims and Hypotheses

The primary aim is to quantitatively assess patient-reported contraceptive nonuse (yes or no) at 3 months (primary outcome).

Hypothesis 1: Contraceptive nonuse will be less likely in the intervention arm than the control arm at 3 months.

The secondary aim is to quantitatively assess the Medical Eligibility Risk category for patient-reported contraceptive method use per the US MEC schema (Category 1=no risk; Category 2=Advantages generally outweigh theoretical or proven risks; Category 3=Theoretical or proven risks usually outweigh advantages; Category 4=unacceptable health risks) [7]. Clinically translated, Categories 1 and 2 indicate methods that are safe to use, Category 3 indicates methods that should be avoided unless more appropriate methods are not available or acceptable to the patient, and Category 4 indicates methods that should be avoided [7]. We will explore the potential impact of the intervention on contraceptive decisions across US MEC categories using qualitative and mixed methods analysis, with a focus on Category 3 cases.

Hypothesis 2: Given the need for a careful and informed discussion to weigh the benefits and risks of Category 3 use, we hypothesize that the decision tool will facilitate this process, leading to more Category 3 use cases in the intervention arm than the control arm.

The exploratory aim is to quantitatively explore contraception decisional conflict measured via a modified Decisional Conflict Scale (DCS) [29], and the patient-reported quality of interaction with their contraceptive provider, as measured via the Interpersonal Quality of Family Planning Scale (IQFP) [30], as mediators of the effects of MHMC on the primary outcome.

Hypothesis 3: The impact of MHMC on contraceptive nonuse will be mediated by lower DCS scores and higher IQFP scores.

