Eligible patients must (1) be aged 18-49 years; (2) be assigned female sex at birth (regardless of gender identity); (3) be able to read in English; (4) have access to a mobile phone, computer, or tablet with internet capabilities; (5) be fertile (have an intact uterus and at least 1 ovary, be premenopausal, have never had permanent contraception surgery, and have no known medical reasons for current infertility, such as use of ovarian suppression medications); (6) have at least 1 index health condition, take an eligible medication, or both (Multimedia Appendix 1; (7) not be currently pregnant; and (8) have a desire to start, switch, or add a contraceptive method for the purpose of preventing pregnancy. Patient exclusion criteria include patients who expect to try getting pregnant in the next 12 months or are presumed infertile for any reason (eg, postmenopausal, hysterectomy, or chemotherapy). During our recruitment process, we explicitly clarify to clinics, clinicians, and patients that transgender patients and postpartum patients are eligible for the trial as long as they meet all other eligibility criteria noted above. Of note, we are developing a Spanish version of the MHMC tool and anticipate expanding eligibility to Spanish-speaking patients in 2026.

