### Patient Study Activities and Quantitative Data Collection

Enrolled patients will complete an electronic baseline survey to report demographics, health history, past and current contraceptive use, contraceptive knowledge, and the secondary and exploratory outcomes (see “Quantitative Outcomes and Analysis” section). To mitigate the risk of differential dropout, recruitment bias, or bias in baseline assessments, we will inform participants of their clinic group assignment after their consent and baseline surveys have been completed [39]. Although this approach entails temporary withholding of information, it is consistent with the Ottawa Statement on the Ethical Design and Conduct of Cluster Randomized Trials [39].

Patients in both the intervention and control arms will receive a web link to a brief video that explains “What to Expect” regarding study activities. Only those in the intervention arm will receive web links to the MHMC tool, a brief video that reviews how to log in and navigate the tool’s features, and a posttool survey to report their experience using MHMC.

The study team will encourage all patients to attend their upcoming clinic visit. Immediately after the clinic visit, patients will receive a postvisit survey and be asked to complete this within 5 days. They will be asked to complete surveys 1 month and 3 months after the clinic visit. Patient surveys require 5-15 minutes to complete. The study team will invite approximately 30 patients who complete study participation to do an optional 1-hour qualitative exit interview by phone or videoconference (refer to “Qualitative Data Collection and Sampling Considerations” section). Patients will receive up to US $100 in cash remuneration for completion of study activities (Figure 4).

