### Quantitative Outcomes and Analysis

The primary outcome is contraceptive nonuse at 3 months per patient self-report, consistent with prior contraceptive studies [10,51,52]. Individual contraceptive nonuse will be modeled as a binary outcome. We will use mixed-effects nested logistic regression to assess differences in 3-month outcomes between the study arms. The model will include an arm assignment categorical covariate and will be adjusted using patient-level covariates (baseline contraceptive nonuse, education, race, ethnicity, and parity) and clinician-level covariates (self-reported experience with contraceptive care and specialty type). Random intercepts for the clinic and for clinicians nested within the clinic will account for the clustering. Secondary analyses of contraceptive nonuse will include the same model with 1-month data and a subgroup analysis that only includes patients at risk for pregnancy, that is, those who report penile-vaginal sexual activity at 1 month and 3 months.

The secondary quantitative outcome is patient-reported contraceptive method use as classified by the US MEC. We will summarize US MEC Categories 1, 2, 3, or 4 among patients who report contraceptive use at 1 month and at 3 months with descriptive statistics. Chi-square tests will be calculated to compare frequencies between the intervention group and the usual care group.

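### Hypothesis 2 is tested only by an unadjusted chi-square that ignores the clinics and the baseline data already collected, so its p-value is unreliable and its estimate is noisier than it need be

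*Protocol article*

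**What the plan says.** Under Quantitative Aims and Hypotheses, Hypothesis 2 expects the tool to improve the discussion of Category 3 methods, "leading to more Category 3 use cases in the intervention arm than the control arm".

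Under Quantitative Outcomes and Analysis, Categories 1 to 4 are summarized "among patients who report contraceptive use at 1 month and at 3 months with descriptive statistics", followed by: "Chi-square tests will be calculated to compare frequencies between the intervention group and the usual care group". No covariate, stratification or clinic term is named. The paragraph before it gives the primary outcome a mixed-effects logistic model with baseline nonuse and other covariates, a random intercept for clinic and another for clinicians nested within clinic.

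Under Patient Study Activities and Quantitative Data Collection, the baseline survey records "health history, past and current contraceptive use, contraceptive knowledge, and the secondary and exploratory outcomes". Baseline category, and whether any method is Category 3 for a given patient, can therefore be derived.

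The patient eligibility criteria ask only that a patient "have at least 1 index health condition, take an eligible medication, or both". They do not require that any method be Category 3 for that patient.

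**The concern.** Two features of this outcome make an unadjusted patient-level test a poor choice.

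- **The outcome depends on baseline.** A patient can be a Category 3 case only if her conditions or medications place some method in Category 3. If she already uses such a method, her follow-up status may simply be carried over. Both facts are known before she learns her clinic's assignment. With seven clinics per arm they can differ between arms by chance, and the stated test cannot take that into account.
- **Patients are grouped in clinics.** The chi-square treats patients from one clinic as independent, in a trial that randomizes clinics and allows for clustering in its sample size and primary model.

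At stake is the trial's only stated quantitative comparison of medical-eligibility category. It could look significant because of the clinic mix, or a real difference could be lost in noise that the collected data would remove.

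**Working it through.** **The plan's own figure.** 14 clinics × 45 = 630, or 315 per arm; 315 × 1.15 = 362.25, rounded up to 363 per arm and 726 in total. This reproduces, but it serves the primary outcome. No rate, power or ICC is given for Category 3 use.

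**Users per clinic.** After 15% attrition, 726 × 0.85 = 617 patients, or 44 per clinic. If 70% use a method (the complement of the 30% baseline nonuse), 617 × 0.70 / 14 = 31. I take 31 to 44, with 36 as a middle value.

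**1. Ignoring the clinics.** The article quotes an ICC of 0.02 from an earlier trial and plans with 0.05. Assume these apply to Category 3 use. Design effect D = 1 + (m − 1) × ICC; the true rejection rate of a nominal 5% test is P(|Z| > 1.96/√D).

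| Users per clinic (m) | ICC | D | Formula | Simulation |
|---|---|---|---|---|
| 31 | 0.02 | 1.60 | 12.1% | 12.4% |
| 31 | 0.05 | 2.50 | 21.5% | 21.8% |
| 44 | 0.02 | 1.86 | 15.1% | 15.1–15.3% |
| 44 | 0.05 | 3.15 | 26.9% | 26.9–27.3% |

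A t test on the 14 clinic proportions stays at about 5% throughout.

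**2. Noise from baseline imbalance.** All inputs here are assumptions: m = 36; a share s of users has a Category 3 option (30%, 50% or 80%); p = 25% of those use one; the ICC of s across clinics is 0.02 to 0.10; a fraction k keeps the baseline method and the rest choose afresh; no tool effect.

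- Variance of a clinic's Category 3 proportion due to availability: A = p² × s(1 − s) × [ICC + (1 − ICC)/m].
- Remaining variance: W = s × p(1 − p)/m.
- Fraction due to availability alone: A/(A + W).
- Fraction due to availability plus baseline use: (A + k²W)/(A + W).

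Example with s = 50%, ICC 0.05, k = 0.5:

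- A = 0.0625 × 0.25 × (0.05 + 0.95/36) = 0.00119.
- W = 0.5 × 0.1875/36 = 0.00260.
- Availability alone: 0.00119/0.00380 = 31%.
- Both: (0.00119 + 0.25 × 0.00260)/0.00380 = 49%.
- SD of the arm difference: √(2/7 × 0.00380) = 3.3 percentage points.

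Simulation of this case gives 30%, 47% and 3.3 points. Over all scenarios the simulated fraction is 9% to 50% for availability alone, and 34% to 63% for both with k = 0.5. The mean arm difference is zero to within 0.1 point. A separate simulation with other assumptions (40–80% with an option, 60% of baseline Category 3 users continuing) gave variance reductions of 34% to 75%.

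**3. What baseline use alone recovers.** The main model below adjusts only for baseline use. If baseline use has the same rate p, its squared clinic-level correlation with follow-up use is [(A + kW)/(A + W)]². For the example this is [(0.00119 + 0.00130)/0.00380]² = 43%; over all scenarios with k = 0.5 it is 30% to 57%. With k = 0 it falls to 1% to 26%. The gain therefore depends mainly on how many patients keep their method.

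**4. Whole arm versus patients with an option.** A 15-point rise among patients with an option, all choosing afresh, is 15 × 0.30 = 4.5, 15 × 0.50 = 7.5 or 15 × 0.80 = 12 points in the whole arm.

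**5. Power, with a 15-point effect among those who choose afresh and k = 0.5.** At s = 30%, 50% and 80%, an unadjusted clinic-level test has 9–13%, 14–17% and 27–30%. Restriction to patients with an option plus baseline adjustment gives 15–18%, 24–27% and 41–42%.

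**The case against.** **Randomization balances case mix in expectation.** This stands. A reader might infer that the comparison mainly measures baseline case mix. The article does not support that: the arm difference centers on zero when the tool has no effect, and the case-mix fraction lies above or below half depending on rates it does not give. Allocation will also attend to the balance of obstetrics and gynecology clinics, which may reduce the imbalance.

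**Dilution is not an error.** This stands too. Hypothesis 2 compares whole arms, so a smaller whole-arm difference is the correct answer to its question. The effect among patients with a Category 3 option is a different estimand and belongs in a supplementary analysis.

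**The share without a Category 3 option is unknown.** The Background says "most people with health conditions are medically eligible to use most methods". A reader might infer that many patients have no Category 3 method, but the sentence is equally compatible with nearly everyone having one or two. Likewise, the Background figure "10%-39% of patients report using combined hormonal contraception (CHC) despite having conditions that may preclude the safe use of CHCs" is not a baseline Category 3 rate: it does not separate Category 3 from Category 4, and it concerns one class of method.

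**Carry-over may be modest.** Patients must want to start, switch or add a method, so fewer than half may keep theirs. Step 3 shows that the gain then shrinks.

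**The excess false positives come from clustering, not from the missing covariate.** Correct: an unadjusted clinic-level test holds its level. Clustering makes the chi-square's p-value wrong; baseline adjustment is about precision. The same sentence of the plan causes both, and one change settles both.

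**The outcome is secondary and serves a mixed methods aim.** True, and no power is claimed for it. That limits the weight of the point but does not justify the weaker test.

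**Conclusion.** The point holds as a weakness in a stated method. At both time points, Hypothesis 2 rests on a chi-square that uses neither the clinic structure nor the baseline information collected. It is not a systematic bias in the estimated difference.

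- **Validity:** the false-positive rate is about 12% to 27% instead of 5%, if the planning ICCs apply to this outcome. In the case-mix model of step 2, where clinics differ only in Category 3 availability, it is 6% to 13% with k = 0.5.
- **Precision:** baseline use and Category 3 availability together account for about one third to two thirds of the chance variation in the arm difference if half of patients keep their method. Availability alone, with nobody keeping a method, accounts for 9% to 50%.
- **Limits:** every Category 3 rate used is assumed. Even the better analysis has low power in these scenarios, so a nonsignificant result should not be read as no effect.

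Whether users only are the right denominator is a separate question, not settled here.

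**What to change.** Replace the chi-square for Hypothesis 2 as follows.

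1. **Main analysis.** At 1 month and at 3 months, regress Category 3 use (yes/no) on arm, with the primary model's random intercepts for clinic and for clinician within clinic, or use a clinic-level analysis. Adjust for Category 3 or 4 use at baseline, derived identically in both arms from baseline-survey conditions, medications and current method; baseline nonusers count as no.
2. **Supplementary analysis.** Report the arm difference among patients whose baseline conditions and medications place at least one method in Category 3, as a baseline-defined subgroup estimate.
3. **Avoid one trap.** Do not enter the has-an-option indicator as a covariate in a logistic model. Patients without an option cannot have the outcome, so its coefficient is not estimable by maximum likelihood. Use restriction or a risk-difference model.
4. **Keep** the four-category table by arm as description.

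The cost is revised wording in the protocol and analysis plan, derivation of baseline categories from survey answers, and a little more analysis work. No extra patients, visits or questions are needed. The change should be fixed before outcomes are examined by arm.

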The exploratory outcomes are hypothesized mediators of the intervention effect on the primary and secondary outcomes. First, contraceptive decisional conflict will be assessed with the DCS, a 16-item validated scale with 4 subscales [29] (0=no conflict; 100=greatest conflict). We slightly modified the wording of DCS items, when appropriate, to reflect contraceptive decisions rather than generic health decisions. Second, we will assess patient-reported quality of interaction with their contraceptive provider via the IQFP [30]. The IQFP contains 11 items that are assigned a score of 1-5 (1=poor, 2=fair, 3=good, 4=very good, and 5=excellent) by the patient to assess their clinician’s shared decision-making and interpersonal skills (total scores ranged from 11 to 55). We will conduct a mediation analysis as described by Baron and Kenny [53] with two models: (1) a logistic regression of the mediator (ie, DCS or IQFS, dichotomized) as a function of the primary outcome (contraceptive nonuse at 3 months), with a covariate for intervention versus control group, and (2) a logistic regression of the primary outcome (contraceptive nonuse at 3 months), adjusting for both the mediator (ie, DCS or IQFPS, dichotomized) and intervention versus usual care group.

We will conduct descriptive analyses on other patient, clinician, and clinic-level exploratory measures and statistical comparison tests as appropriate (eg, chi-square, Fisher exact, and *t* tests).

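### Mediation model 1 regresses the mediator on the 3-month outcome, so no stated model validly estimates the arm-to-mediator leg of Hypothesis 3

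*Protocol article*

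**What the plan says.** Hypothesis 3, under Quantitative Aims and Hypotheses, reads: "The impact of MHMC on contraceptive nonuse will be mediated by lower DCS scores and higher IQFP scores". The section Quantitative Outcomes and Analysis then sets out the method: "We will conduct a mediation analysis as described by Baron and Kenny [53] with two models".

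- Model 1 is "a logistic regression of the mediator (ie, DCS or IQFS, dichotomized) as a function of the primary outcome" at 3 months, "with a covariate for intervention versus control group".
- Model 2 is "a logistic regression of the primary outcome (contraceptive nonuse at 3 months), adjusting for both the mediator" (again dichotomized) and study arm.

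The same section gives the primary analysis: "We will use mixed-effects nested logistic regression to assess differences in 3-month outcomes between the study arms". Further exploratory comparisons are promised only for measures other than these two scales: "We will conduct descriptive analyses on other patient, clinician, and clinic-level exploratory measures and statistical comparison tests as appropriate".

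**The concern.** Hypothesis 3 describes a chain in which arm changes decisional conflict or interaction quality, and that change alters nonuse. Showing it needs three things: the effect of arm on nonuse, the effect of arm on the mediator, and the association of mediator with nonuse given arm. The sequence named in the article has the same three steps.

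Model 1 is where the arm-to-mediator step should be. Instead the 3-month outcome is the predictor of its own hypothesized mediator, and arm is adjusted for that outcome. Under Hypothesis 3, nonuse at 3 months is a consequence of both arm and mediator. Conditioning on it mixes the arm-mediator effect with an association created by the conditioning. The arm coefficient of model 1 could then be read as the effect of the tool on decisional conflict or interaction quality when it is not.

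**Working it through.** The article gives no figure for the mediation analysis, so there is nothing to reproduce. The check sets the stated models against the required steps and then sizes the bias.

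**Which step does each stated model supply?**

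| Step | Stated model | Supplied? |
|---|---|---|
| Nonuse on arm (total effect) | Primary mixed-effects logistic model | Yes |
| Mediator on arm | None; model 1 adds 3-month nonuse as predictor | No |
| Nonuse on mediator and arm | Model 2 | Yes |

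**What model 1 estimates.** Let X be arm, M the dichotomized mediator (1 = favourable: low conflict or high quality) and Y nonuse. Suppose logit P(M=1|X) = m + aX and logit P(Y=1|M,X) = i + bM + cX. Write q(x,m) = 1 - P(Y=1|x,m). By Bayes' rule:

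logit P(M=1|Y,X) = m + aX + bY + ln[q(X,1)/q(X,0)]

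Two results follow.

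1. The coefficient of Y in model 1 is b, which is also the mediator coefficient in model 2. Model 1 adds nothing on that link.
2. The arm coefficient of model 1 is a + ln[q(1,1)/q(1,0)] - ln[q(0,1)/q(0,0)], not a. The extra term vanishes if b = 0 or c = 0. Bias needs both a mediator-outcome association and a direct effect.

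**Inputs.** Control nonuse is set near 30%. The article gives 30% for baseline, so using it at 3 months is an assumption. Control mediator prevalence of 50% (m = 0) and the values of a, b and c are also assumptions. Clustering is ignored.

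**Worked case, a = 0, b = -1.5, c = -1.3, i = -0.20.**
- q(0,0) = 0.5498, q(0,1) = 0.8455, q(1,0) = 0.8176, q(1,1) = 0.9526.
- Control nonuse = 1 - (0.5498 + 0.8455)/2 = 30.2%; MHMC nonuse = 1 - (0.8176 + 0.9526)/2 = 11.5%.
- Arm coefficient = 0 + ln(0.9526/0.8176) - ln(0.8455/0.5498) = 0.153 - 0.430 = -0.28.

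**Range** (i = -0.20 for b = -1.5, and i = -0.51 for b = -0.7, which keeps control nonuse at 30.2%):

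| True a | c | b | MHMC nonuse | Model 1 arm coefficient |
|---|---|---|---|---|
| 0 | -1.3 | -1.5 | 11.5% | -0.28 |
| 0 | -1.3 | -0.7 | 10.8% | -0.14 |
| 0.70 | -1.0 | -1.5 | 11.9% | 0.47 (33% too small) |
| 0.70 | -1.0 | -0.7 | 12.6% | 0.59 (16% too small) |
| 0.70 | 0 | -1.5 | 25.2% | 0.70 (no bias) |

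With b = 0 and c = -1.4 the arm coefficient is 0.00 for a true 0, so again there is no bias. Regressing M on X alone returns a in every row.

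**Error rates.** A separate simulation used 2,000 trials per scenario with 7 x 45 = 315 patients per arm, nonuse of 30% versus 10% (the 20% target difference read as absolute) and a two-sided 0.05 test. Here the mediator is coded as the unfavourable state, so a helpful effect of arm is an odds ratio below 1.

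| True arm-mediator OR | Mediator-outcome OR | Model 1 arm test rejects | Mediator-on-arm test rejects |
|---|---|---|---|
| 1.00 | 3 | 26% | 5% |
| 1.00 | 5 | 45% | 5% |
| 0.67 | 3 | 20% | 68% |
| 0.67 | 5 | 9% | 71% |

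In the two null rows the exact model 1 odds ratios are 1.24 and 1.37, so the spurious effect points away from Hypothesis 3.

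**The case against.** The strongest reply is that this is probably a transposition in drafting. The article names a standard method whose mediator step has arm as the predictor, and an analyst following that method would fit the right model. That may be so. But the sentence names the dependent variable and the predictor explicitly, and nothing else in the article corrects it.

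The second reply is about weight, and it stands. The aim is labelled exploratory, and the primary model, sample size, randomization and data collection are untouched.

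The third is that the size depends on inputs the documents do not give. That also stands, which is why a range is shown. The bias is zero if the effect runs wholly through the mediator or if the mediator is unrelated to nonuse. Relying on either would assume what the analysis is meant to examine.

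Several stronger readings are tempting and are not supported:

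- A reader might infer that Hypothesis 3 cannot be tested at all. Model 2 gives the direct effect and the mediator-outcome link, the primary model gives the total effect, and only one leg is missing. Respecifying model 1 supplies it.
- A reader might infer that the error would manufacture support for mediation. In the scenarios above, with a beneficial direct effect, it works against Hypothesis 3 by shrinking or reversing the arm-mediator effect.
- A reader might count the absence of clinic terms in the mediation models as a further error. An article may leave such terms to the analysis plan, which is not shown.
- Dichotomizing the two scores loses information, but it is a choice and does not invalidate the analysis. No cut-point or distribution is given from which to size the loss.

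**Conclusion.** The point holds in this form: model 1 as written reverses mediator and outcome, contrary to the method it cites, and no stated model validly estimates the effect of arm on decisional conflict or interaction quality. That the nonuse coefficient duplicates model 2, and that the arm coefficient is biased when b and c are both nonzero, follows algebraically under logistic models with a binary mediator and no arm-by-mediator interaction.

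The size is conditional. Over the assumed range, the arm log odds ratio is shifted by about -0.14 to -0.28 when the truth is 0, and by about -0.11 to -0.23 when the truth is 0.70. The rejection rates rest on the same kind of assumption and on unclustered data, so they are illustrative.

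This is a should-fix. The claim about mechanism is affected; the primary conclusion on nonuse is not.

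**What to change.** Respecify model 1 as the mediator (DCS or IQFP) regressed on study arm, without 3-month nonuse as a predictor. Adjust for the baseline score where it was collected, and use the same clustering terms as the primary model (clinic, and clinician within clinic). Keep model 2 as stated, and name the primary analysis as the total-effect step.

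State which survey supplies the mediator. It should be measured after the intervention and before the 3-month outcome. The text places the exploratory outcomes in the baseline survey and does not say which follow-up survey carries them. The flow figures are not available here, so this needs confirming.

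Keeping the scores continuous is an optional gain in precision. If they stay dichotomized, the corrected model 1 remains a logistic regression.

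The cost is a sentence or two of protocol or analysis plan wording and minor programming. No new data are needed. The change should be recorded before 3-month outcomes are examined by arm.
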